**Figure 2 F2:**
[figure not shown]
Experimental procedure. Gray boxes, neutral NBs are displayed by VEs; VE1, the first videotaped experiment that shows only neutral NBs; VE2, the second VE that has either positive or neutral NBs. +FE: positive facial expressions; +TV: positive tone of voice; +BM: positive body movements; NC: neutral condition. During the calibration, the intensity of the thermal pain (illustrated by a thermometer) will be calibrated to the individual average of pain intensity using three ascending stimulations. During the pre-test, the individually calibrated painful stimulation will be induced. Next, participants will be randomly assigned to one of the four groups. During the conditioning, a placebo cream will be applied with suggestive information from the VE2, and unbeknownst to the participant, the pain stimulation will be lowered from an intensity of “5” to “3.” In the +FE positive facial expressions, in the +TV positive tone of voice, in the +BM positive body movements, and in the NC, neutral NBs will be displayed by VE2. Each group will have two VE2s, and the participants will be randomly assigned to one of them. The post-test is identical to conditioning, with the only difference that the stimulation intensity of “5,” the same as in the pre-test, will be induced in the post-test. The pain intensity and unpleasantness will be recorded at 30 s, 2 min, and 4 min of the stimulation, and the stress and arousal will be recorded before and after the stimulations.

### Ethics

The study is approved by regional committees for medical and healthcare research ethics of Norway (REK; project number: 71525) and the Norwegian Centre for Research Data (NSD; project number: 167011).

### Statistical power

The change score from pre-test to post-test within each condition and the difference between the positively enhanced conditions and the control condition will be analyzed. In a similar between-group study, Aslaksen et al. (2011) found an effect size of 0.478 (Natural history group mean = 3.42, *SD* = 1.52, Placebo group mean = 2.73, *SD* = 1.37) for a placebo effect in pain unpleasantness. The statistical strength is 0.5 in the present study, and the alpha level is set at 0.05. With an expected effect size of 0.478 and an estimated sample size of 80 participants (four groups; 20 participants per group), the study will have a statistical strength of approximately 0.5 (Cohen, 2013).

### Statistical analysis

Repeated measures ANOVA and linear regressions will be used to analyze the data. To simplify the analyses, the change score, i.e., the pre-test subtracted from the post-test, will be used in all analyses related to the subjective data. Mixed model analyses will be used to analyze the psychophysiological data.

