### Design

We propose a mixed design with four Groups (+FE, +TV, +BM, and NC; as between factors) × 3 Timepoints (first at 30 s, second at 2 min, and third timepoint at 4 min of the stimulation), with the covariate effects of participant sex with two levels, and the knowledge of the assistants with two levels (CI and UI).

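### The NB group comparisons use raw change scores without the pre-test as covariate, which may lose precision at no saving

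*Protocol article*

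**What the plan says.** The Statistical analysis section plans repeated measures ANOVA and linear regressions. It states that "the change score, i.e., the pre-test subtracted from the post-test, will be used in all analyses related to the subjective data", and simplicity is the only reason given. The Statistical power section frames the analysis in the same way: "The change score from pre-test to post-test within each condition and the difference between the positively enhanced conditions and the control condition will be analyzed".

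The Design section describes four groups by three timepoints, "with the covariate effects of participant sex with two levels, and the knowledge of the assistants with two levels". The pre-test score is not among the covariates.

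The Figure 2 legend places the pre-test stimulation first and then says: "Next, participants will be randomly assigned to one of the four groups". Until that point only the first videotaped experimenter, who shows neutral behaviour, has been on screen.

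**The concern.** Analysing post minus pre with no further adjustment assumes that each extra point at pre-test carries over as exactly one extra point at post-test. If the true slope is below 1, subtraction over-corrects and part of the pre-test variation is added to the outcome as noise. Including the pre-test as a covariate lets the data set the slope. It also adjusts properly for pre-test differences that arise by chance, which are to be expected with 20 per group.

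At stake is the precision of the NB group contrasts behind aims 1, 2 and 4 (for aim 4, the subjective stress ratings). The plan itself expects power of only about 0.5, so precision given up for simplicity matters more than it would in a larger study. An unseen analysis plan does not settle this, because the article states the choice outright for all subjective data.

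**Working it through.** **Inputs from the article (Statistical power).** "Natural history group mean = 3.42, *SD* = 1.52, Placebo group mean = 2.73, *SD* = 1.37"; "With an expected effect size of 0.478 and an estimated sample size of 80 participants (four groups; 20 participants per group"; "the alpha level is set at 0.05". Sidedness is not stated; I take two-sided.

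**The plan's own figures.** The difference is 3.42 − 2.73 = 0.69. The pooled SD is √((1.52² + 1.37²)/2) = 1.447, so d = 0.69/1.447 = 0.477; with the simple mean of the two SDs, 1.445, it is 0.478. The effect size reproduces. The power of about 0.5 does not: noncentral t gives 0.31 for 20 v 20 and 0.45 for 60 v 20 (three positive groups pooled against neutral). That is a separate matter and the present point does not depend on it.

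**Assumed inputs.** r, the pre-post correlation, 0.3 to 0.7; k = pre-test SD / post-test SD, 0.5 to 1; no dropout. The article gives none of these.

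**Variances, in units of the post-test variance.**
- Change score: 1 + k² − 2rk
- Adjusted for pre-test: 1 − r²
- Difference: (1 + k² − 2rk) − (1 − r²) = (k − r)²
- Variance ratio, adjusted to change: (1 − r²)/(1 + k² − 2rk)
- Gain in effective sample size: (k − r)²/(1 − r²)

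The gain is a square over a positive number, so it cannot be negative, and it is zero only when r = k. The sole cost is one degree of freedom.

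Example, r = 0.3 and k = 1: change variance 1 + 1 − 0.6 = 1.40; adjusted variance 1 − 0.09 = 0.91; ratio 0.65; gain 0.49/0.91 = 54%.

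**Power.** Noncentral t, two-sided 0.05, reading 0.478 as an effect on the raw post-test scale: d = 0.478/√(change variance) against 0.478/√(adjusted variance), with one degree of freedom charged to the adjusted analysis.

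| k | r | Variance ratio | Gain in effective n | Power 20 v 20, change → adjusted |
|---|---|---|---|---|
| 1 | 0.3 | 0.65 | 54% | 0.24 → 0.34 |
| 1 | 0.5 | 0.75 | 33% | 0.31 → 0.40 |
| 1 | 0.7 | 0.85 | 18% | 0.48 → 0.54 |
| 0.75 | 0.3 | 0.82 | 22% | 0.29 → 0.34 |
| 0.75 | 0.5 | 0.92 | 8% | 0.37 → 0.40 |
| 0.75 | 0.7 | 0.995 | 0.5% | 0.54 → 0.54 |
| 0.5 | 0.3 | 0.96 | 4% | 0.33 → 0.34 |
| 0.5 | 0.5 | 1.00 | 0% | 0.40 → 0.40 |
| 0.5 | 0.7 | 0.93 | 8% | 0.51 → 0.54 |

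The article does not say whether the cited SDs are of ratings or of changes. If 0.478 is already an effect on the change scale, the starting power for 20 v 20 is 0.31 throughout. At k = 1 it then rises to 0.45, 0.40 and 0.36 for r = 0.3, 0.5 and 0.7. The percentage gains in the table are unaffected.

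**Same contrast from either outcome.** If post = a + b·pre + group effect, then post − pre = a + (b − 1)·pre + group effect. Only the pre-test coefficient changes. With the pre-test mean as covariate, this holds for the group effect averaged over the three timepoints.

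**The case against.** The strongest reply is that the gain may be small. The stimulus is individually calibrated to a rating of 5, which may narrow the spread of pre-test pain ratings. If k is well below 1, most of the gain disappears: at k = 0.5 it is at most 8% over this range of r. A reader might take the equal-SD gains of 18% to 54% as the expected benefit; the article does not support that, and they are only the top rows of the table. Nor does it support the rule that a change score is noisier than the post-test alone whenever r is below 0.5. The general threshold is r < k/2, which is 0.375 at k = 0.75 and 0.25 at k = 0.5.

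The likely size of r is also open. Calibration uses brief ascending ramps, whereas the pre-test is a four-minute constant stimulus rated three times. Stable individual differences may persist, and averaging three ratings reduces noise. Stress and arousal are not calibrated at all.

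A reader might further infer that the planned analysis is biased, for instance by regression to the mean. It is not: groups are randomised, so regression to the mean is expected equally in every arm.

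Finally, replacing change scores altogether would harm the plan. The change within each condition (Statistical power) and aim 3, which links pain reduction to stress, both need them.

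All of this stands, and it limits the size of the point and the form of the remedy. It does not justify fixing the slope at 1, since uncertainty about r and k is a reason to estimate the slope.

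**Conclusion.** The concern holds as one of precision, not validity. The plan fixes an unadjusted change score for the subjective outcomes although a baseline recorded before group assignment is available. Over r = 0.3 to 0.7 and k = 0.5 to 1, the loss is equivalent to between about 0% and 54% of effective sample size. Both parameters are assumptions, and the article does not allow the range to be narrowed.

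Adjustment does not make the study well powered: the highest adjusted 20 v 20 power in the table is 0.54.

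The conclusion covers outcomes with a pre-test value: pain intensity, unpleasantness, stress and arousal. CARE and expected efficacy have none. It also concerns the NB comparison only. For the exploratory hypotheses on assistant information, the assistant is already in the room at the pre-test, so the pre-test may not be a pre-exposure baseline there.

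**What to change.** Add a sentence to the Statistical analysis section, and the matching entry to the Design section: for NB group comparisons of pain intensity, unpleasantness, stress and arousal, the change score is the outcome and the participant's corresponding pre-test score is a covariate beside sex and assistant knowledge. For the two pain ratings, use the mean of the three pre-test ratings.

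Keep the unadjusted change score for the change within each condition and for aim 3. For the assistant-information hypotheses, state that the pre-test may already reflect the assistant's presence, and interpret any pre-test adjustment there accordingly.

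The cost is one sentence and one degree of freedom per model, with no new data.

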### Design

We propose a mixed design with four Groups (+FE, +TV, +BM, and NC; as between factors) × 3 Timepoints (first at 30 s, second at 2 min, and third timepoint at 4 min of the stimulation), with the covariate effects of participant sex with two levels, and the knowledge of the assistants with two levels (CI and UI).

### Expected results

Three main results are expected: First, the administration of the placebo cream with the suggestive information and conditioning will result in reduction in pain and a placebo effect in all groups. Second, the amplitude of the placebo effect will be lowest in the NC compared to other groups, and lastly, the +FE will have the largest reduction in pain and placebo effect compared to other groups. Moreover, the NC will have higher stress levels (both subjective and physiological) than the other groups, and the +FE will have the lowest stress levels. Facial expressions are perhaps the most important NBs in the transmission of treatment-related expectations and beliefs from providers to the care seeker. It has been shown that the facial expressions of healthcare providers signal what expectations the doctors hold about the treatment (Valentini et al., 2014; Chen et al., 2019).

Regarding the effects of assistant expectations, it is expected that the CI assistants elicit larger placebo analgesic effects and lower stress levels compared to the UI assistants (Kaptchuk, 2001).

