In this experiment, all groups will receive a placebo treatment and verbal suggestions about the treatment. As there is no control group with no treatment in this design, we may not be able to exclude the reduction in pain to a placebo effect (Flaten et al., 2013). However, this design was chosen because the aim of the study was to investigate the effects of caregivers' NBs on pain reports and placebo effects. To test the effects of a factor on placebo effects, previous studies have used similar designs with no natural history control group (Flaten et al., 2006; Dutt-Gupta et al., 2007; Varelmann et al., 2010). As all groups will receive treatment plus verbal suggestions, a reduction in pain is expected in all groups. The NBs of the videotaped experimenters are the only factor that is different between the groups; thus, any difference in the reduced pain between the groups can be attributed to the non-verbal manipulations.

To strengthen the placebo effects, a conditioning procedure was also added. It has been shown that verbal suggestion about a treatment plus conditioning can enhance the generation of placebo effects (e.g., Colloca et al., 2008; Flaten et al., 2013).

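### A placebo effect in all groups is the first expected result, but every group gets the cream, so within-group pre-to-post change cannot identify one

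*Protocol article*

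**What the plan says.** All references are to the Protocol article.

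- **Expected results.** The first of three main results is that cream, suggestion and conditioning "will result in reduction in pain and a placebo effect in all groups". The second and third compare groups: smallest placebo effect in the neutral condition, largest with positive facial expressions.
- **Statistical power.** Two quantities are to be analysed: "The change score from pre-test to post-test within each condition", and the difference between the positive conditions and the control condition.
- **Statistical analysis.** There is one subjective outcome: "the change score, i.e., the pre-test subtracted from the post-test, will be used in all analyses related to the subjective data".
- **Procedure and Figure 2.** Every participant has a 4-minute pre-test at level 5, then cream and a conditioning stimulation at level 3, then a post-test in which "the stimulation intensity of “5,” the same as in the pre-test, will be induced in the post-test". The order is the same for everyone.
- **General discussion.** It states that "all groups will receive a placebo treatment and verbal suggestions about the treatment", and that for lack of an untreated control "we may not be able to exclude the reduction in pain to a placebo effect". It then defends the design for a different contrast: "any difference in the reduced pain between the groups can be attributed to the non-verbal manipulations".
- **Expected limitations.** The first videotaped experimenter plays the neutral phases before conditioning. The second plays both conditioning and post-test.

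**The concern.** A placebo effect is the part of the pain reduction that would be absent without the placebo treatment. Measuring it needs something untreated to compare with. Here no group, skin site or test sequence goes without the cream, and the neutral condition, called the control, gets the full placebo procedure. The pre-to-post change in any one group is therefore a total that includes whatever repeated heat stimulation does to ratings by itself.

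The General discussion recognises this, while the Expected results section still names the total a placebo effect and puts it first among the main results. A reader who follows the Statistical power and Expected results sections as written could take a significant within-group fall as confirming placebo analgesia in that group, which the design cannot show. Since only one subjective change score is defined, pain reduction and placebo effect are two names for the same number.

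**Working it through.** **1. The plan's own figure.** The effect size in Statistical power is reproduced from its stated inputs: (3.42 − 2.73) / √[(1.52² + 1.37²)/2] = 0.69 / 1.447 = 0.477, against 0.478 in the text. It comes from a natural-history group compared with a placebo group, a contrast this trial does not contain. The stated power of about 0.5 is a separate matter and is not used here.

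**2. What the change contains.** Write the mean reduction in group g (pre-test minus post-test, the plan's score with its sign reversed) as

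reduction(g) = drift + placebo(g) + direct(g)

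Drift is any habituation, sensitisation or order effect of repeated stimulation. Placebo(g) is the effect of cream, suggestion and conditioning. Direct(g) is any effect on the pain rating of the behaviours on screen during the post-test.

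- *Within a group:* one observed mean and three unknowns. A larger sample sharpens the mean but does not separate the parts.
- *Between a positive group and the neutral condition:* drift common to the groups cancels in expectation under randomisation. What remains is [placebo(g) − placebo(NC)] + [direct(g) − direct(NC)]. This can be credited to the non-verbal behaviours, as the General discussion says, but the two brackets cannot be told apart.

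The direct route is not far-fetched on the document's own terms. The Introduction describes positive caregiver behaviours both as lowering pain and as increasing placebo effects, and the second experimenter's behaviours are on screen in the post-test.

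**3. Illustration of size.** The document gives neither a drift nor an SD of change, so both are assumed. Set the placebo and direct effects to zero and use a two-sided paired t test at 0.05 in one group of 20. With noncentrality λ = (drift / SD) × √20, the probability of a significant reduction is P(T > 2.093), where T is noncentral t with 19 degrees of freedom.

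| Assumed drift | SD of change | λ | Probability, one group of 20 |
|---|---|---|---|
| 0 | any | 0 | 0.025 |
| 0.5 | 1.0 | 2.236 | 0.56 |
| 0.5 | 1.5 | 1.491 | 0.29 |
| 0.5 | 2.0 | 1.118 | 0.19 |
| 1.0 | 1.0 | 4.472 | 0.99 |
| 1.0 | 1.5 | 2.981 | 0.81 |
| 1.0 | 2.0 | 2.236 | 0.56 |

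The prediction concerns all four groups. The chance that all four are significant together is the fourth power of the last column. Over the six rows with drift it runs from about 0.001 (0.185⁴) to about 0.96. The table covers drift toward lower ratings. Sensitisation would act the other way and could hide a real placebo effect.

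**The case against.** The strongest reply is that the authors already say this. The General discussion discloses the missing untreated group and limits the inference to group differences. The Expected results section is a list of predictions, not an analysis rule. Aims 1, 2 and 4 compare groups, aim 3 is an association, hypothesis 5 compares types of assistant, and the Design section sets out a comparison of groups over timepoints. Pain report is also a declared objective, so a direct effect of the behaviours on ratings is within scope.

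Most of this stands, and it rules out several stronger readings that a reader might infer:

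- *That the analysis as a whole rests on the wrong contrast.* It does not. The planned comparisons are mainly between groups, and this point leaves the randomised ones intact.
- *That the plan commits to reporting a significant within-group fall as placebo analgesia.* It nowhere says so. The risk comes from the prediction and the planned within-condition analysis taken together.
- *That regression to the mean inflates the change.* The document gives little support. The temperature is set in a separate calibration before the pre-test, and participants are not selected on a pain score.
- *That the probabilities above estimate the error.* They do not. Drift and SD are assumed, and the direction of any drift is unknown.

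What the reply does not remove is the conflict itself. A limitation stated in the General discussion does not correct a contrary statement listed first among the main results.

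**Conclusion.** The point holds as a contradiction in the Protocol article with a clear consequence for interpretation. The Expected results and Statistical power sections invite a conclusion, a placebo effect in each group, that the design cannot identify and that the General discussion says may not be available. This follows from the design and needs no numerical assumption. Only the illustrated range of about 0.19 to 0.99 per group of 20 depends on the assumed drift, SD and zero placebo effect.

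The randomised between-group differences for aims 1 and 2 remain valid as effects of the non-verbal behaviours on change in reported pain. Whether such a difference is a changed placebo effect, a direct effect on pain report, or both, is a caveat on interpretation and not a fault in the comparison.

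**What to change.** Bring the Statistical power and Expected results sections into line with the General discussion:

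1. Word the first expected result as a reduction in reported pain under the placebo cream in all groups.
2. State that within-group change will be reported descriptively and not as evidence of a placebo effect.
3. Rest the conclusions for aims 1 and 2 on randomised between-group differences in that change. Keep hypothesis 5 as an exploratory comparison of assistant types.
4. Add that, because the second experimenter's behaviours are also shown during the post-test, a group difference may reflect a direct effect on pain report, modulation of a placebo effect, or both.

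The cost is a few sentences, with no change to sample size, procedures or data collection. The downside is a narrower claim.

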### Preparatory study

As a proof of concept, we tested the reliability (i.e., inter-rater reliability and internal consistency) and validity (i.e., construct validity) of the NB videos before the experiment was conducted. We tested the construct validity of NBs, i.e., that the expressed NBs are the NBs that were intended to be expressed. We asked two groups of Norwegian and US psychology students to code the NB videos based on a NB rating scale we developed. The hypotheses tested were: (a) the coding of NBs was consistent across coders (i.e., inter-rater reliability); (b) the NB manipulations were enhanced or diminished as they were intended to (i.e., construct validity of NBs); the NBs were rated similarly across actors (i.e., reliability); (c) the NB ratings were rated similarly by the Norwegian and the US coders, and (d) micro-level NBs (smile, eye contact, etc.) contributed to the macro-level ratings of dominance, positivity, and expressivity.

### NB coders

Fifteen Norwegian (11 females, 4 males; Mean age = 22.8; *SD* = 1.28) and six US (5 females, 1 male; Mean age = 21.3; *SD* = 1.54) undergraduate psychology students performed the coding. The Norwegian students performed the coding as part of their course “Bachelor Thesis in Psychology” at NTNU, in the spring semester of 2021. The US students were research assistants working in the second author's laboratory for course credit in the spring semester of 2021. The coders received training on how to use the coding log and perform the coding. The NB coding task can be done with a minimum of two coders (van Osch et al., 2017; Blanch-Hartigan et al., 2018); however, in this study, 21 coders from two different cultures were recruited.

